### Outcomes

The primary outcome for the first aim will be the performance of the AIm-PBC disease activity index compared to conventional monitoring strategies. This will be assessed through its calibration against established risk scores such as UK-PBC and GLOBE [22,23], as well as its responsiveness to clinically meaningful changes in disease activity. The ability of the integrated symptom indexes to correlate with biochemical progression or regression will also be evaluated, providing insights into whether the inclusion of PROs enhances the sensitivity of disease monitoring. Explainability will be measured via the interpretability of SHAP-based visualizations and their perceived clinical utility during clinician evaluations.

For the second aim, the primary outcome will be the discriminatory ability of the multi-signal predictive model to identify patients at high risk of CSPH and early complications such as variceal hemorrhage or ascites. This will be quantified using the area under the receiver operating characteristic curve (AUROC), with additional measures of calibration and clinical utility assessed through decision curve analysis and net reclassification improvement. Comparative analyses will determine whether the composite model outperforms single-modality rules and consensus criteria such as Baveno VII, and subgroup analyses will explore performance consistency across patients with AIH overlap and MASH.

For the third aim, the primary outcome will be the effectiveness and usability of the EHR-integrated CDS prototype. Effectiveness will be measured via improvements in clinician adherence to guideline-concordant care pathways, including pruritus management, bone health interventions, and risk-based endoscopy referrals. Usability will be assessed using the System Usability Scale, with a target score of 70 or higher, and cognitive load will be evaluated using the NASA-Task Load Index. Clinician trust in the AI system will be measured through the AI trust scale, whereas decision accuracy and decision time will be compared between CDS-assisted and usual care conditions during the randomized crossover simulation. Feasibility indicators, including recruitment and completion rates, will be monitored during the pragmatic pilot phase.

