### Randomization

Randomization will apply only to the implementation phase of the study during the clinician-level crossover simulation. Clinicians will be randomly assigned in a 1:1 ratio to 1 of 2 sequences: usual care followed by CDS-assisted care or CDS-assisted care followed by usual care. A computer-generated randomization schedule will be used to balance allocation between sequences and minimize allocation bias. The simulation will use standardized, deidentified cases rather than live clinical encounters.

To minimize learning and carryover effects, the 2 simulation periods will use distinct, nonoverlapping standardized cases matched in clinical complexity. A 1-week washout period will separate the 2 conditions, and case order will be varied within each period where feasible. Primary comparisons will be conducted within clinicians, allowing each participant to serve as their own control (Figure 2).

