For the third aim, implementation outcomes will be analyzed using both descriptive and inferential methods. Usability scores from the System Usability Scale (Multimedia Appendix 1), clinician trust scores from the AI trust scale adapted for AIm-PBC (Multimedia Appendix 2), and cognitive load measures from the National Aeronautics and Space Administration Task Load Index (Multimedia Appendix 3) will be summarized and compared between CDS-assisted and usual care conditions. Decision accuracy and decision time will be analyzed using 2-tailed paired *t* tests within the randomized crossover simulation, whereas clinician adherence to guideline-concordant care pathways will be evaluated using within-clinician comparisons across study phases. Feasibility indicators, such as recruitment and completion rates, will be reported as proportions with CIs. Qualitative debriefing interviews will be analyzed to explore clinician perceptions of usability, workflow integration, trust, and barriers to implementation (Multimedia Appendix 4). Fairness metrics, including AUROC parity gaps across demographic and clinical subgroups, will be calculated to ensure equitable performance of the CDS tool.

All analyses will be conducted using validated statistical software packages in R (R Foundation for Statistical Computing) and Python (Python Software Foundation), with significance thresholds set at a 2-sided α value of .05. Missing data will be addressed through multiple imputation techniques, and sensitivity analyses will be performed to confirm the robustness of the findings.

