## Results

At the time of manuscript submission, this protocol had not yet begun participant recruitment or data analysis. No participants had been recruited. The study did not receive external funding; therefore, no funding date is applicable. Data collection is projected to begin after institutional review board approval and ClinicalTrials.gov registration, with retrospective data extraction and prospective observational data collection expected to occur over approximately 24 months. The clinician-level randomized crossover simulation and pragmatic pilot implementation phases are expected to occur after model development and validation are completed. Data analysis will begin after completion of the relevant data collection phases. The main study findings are expected to be submitted for publication in summer 2029.

The integrated disease activity index is expected to show strong calibration with established prognostic scores and greater responsiveness to clinically meaningful changes, whereas the inclusion of PROs will provide a more comprehensive view of symptom burden. The predictive model is expected to achieve an AUROC of at least 0.85 for identifying CSPH and deliver a net reclassification improvement of 10% or more over Baveno VII criteria, reducing unnecessary endoscopies without compromising safety. Finally, the CDS prototype is expected to improve clinician adherence to guideline-concordant care pathways, reduce decision time, and achieve high usability and trust scores during the simulation and pilot phases.

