## Discussion

### Principal Results

This protocol describes a multiphase study aimed at improving the management of PBC through an explainable AI framework. The anticipated results include a dynamic disease activity index that integrates biochemical, elastography, and patient-reported data, offering superior responsiveness and calibration compared to conventional monitoring. The predictive model is expected to achieve high discrimination for CSPH and outperform existing criteria, reducing unnecessary endoscopies while maintaining patient safety. Finally, the CDS prototype is designed to enhance clinician adherence to guideline-based care, improve decision accuracy, and reduce cognitive load, with usability and trust scores meeting or exceeding established benchmarks.

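### The simulation's overall accuracy average and its trust scores cannot separate appropriate from indiscriminate reliance on the tool, because the share of wrong-output cases is not controlled: a cheap improvement

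*Protocol article*

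**What the plan says.** **Accuracy.** Under the third aim, the Outcomes section states that "decision accuracy and decision time will be compared between CDS-assisted and usual care conditions during the randomized crossover simulation". The Statistical Analysis section gives the method: "Decision accuracy and decision time will be analyzed using 2-tailed paired" t tests within the simulation. Neither section splits the comparison by whether the tool's output was right.

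**Trust.** The Outcomes section states that "Clinician trust in the AI system will be measured through the AI trust scale". Statistical Analysis has the scores summarised and compared by condition. The Results section expects the prototype to "achieve high usability and trust scores during the simulation and pilot phases", and Principal Results describes a tool meant to "improve decision accuracy, and reduce cognitive load, with usability and trust scores meeting or exceeding established benchmarks". Higher is read as better, with no link to correctness. No trust threshold is given.

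**Cases.** The Randomization section says: "The simulation will use standardized, deidentified cases rather than live clinical encounters". The two periods use different cases of similar complexity. The Harms section allows synthetic as well as deidentified data. Complexity is the only matching feature named, and the share of cases with a wrong output is not fixed.

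**Fallibility of the tool.** The Results section says: "The predictive model is expected to achieve an AUROC of at least 0.85 for identifying CSPH". Some outputs will therefore be wrong. The Interventions section describes dual-threshold triage cues and order sets that also cover pruritus and bone health.

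**Nearest safeguards.** Ethical Considerations provides for general monitoring of safety and unintended consequences. Statistical Analysis plans debriefing interviews that touch on trust. Neither measures how often clinicians follow a wrong output.

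**The concern.** Reliance on a decision aid helps where its output is right and hurts where it is wrong. An overall average mixes the two in proportions set by whoever picks the cases. A case set with few wrong outputs shows a large gain, and one with many shows a small gain or a loss, even if clinicians behave identically. Two groups with the same average can also differ sharply in what they do when the tool errs.

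A trust score read as better when higher does not resolve this, because it does not ask whether the trust was warranted.

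The simulation comes before use in live visits, and its standardised cases can be scored against a known answer. It is therefore the natural place to measure reliance on wrong outputs. If the case set contains too few of them, no later analysis of the same data can recover the information.

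**Working it through.** **Inputs from the protocol:** about 24 clinicians, chosen pragmatically (Recruitment); 1:1 allocation to two sequences (Randomization); paired t test, two-sided alpha 0.05 (Statistical Analysis). No effect size, standard deviation, power, number of cases, unaided accuracy or reliance rate is given for the simulation, so there is no stated figure to reproduce. Every value below is assumed.

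**Notation:** u = unaided accuracy, taken as equal in right-output and wrong-output cases; q = share of simulated cases in which the tool's output is right; r = probability that the clinician follows the output regardless of its correctness.

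**Step 1. Gain in each type of case.**
- Output right: assisted accuracy is r + (1 - r)u, so the gain is r(1 - u).
- Output wrong: assisted accuracy is (1 - r)u, so the gain is -ru.

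**Step 2. Average gain.** q·r(1 - u) - (1 - q)·ru = r(q - u). The sign is set by q relative to u. When q > u, the average rises with indiscriminate reliance r. When q < u, it falls.

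**Step 3. Numbers with u = 0.70 (percentage points).**

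| q | r = 0.90 | r = 0.30 |
|---|---|---|
| 0.5 | -18 | -6 |
| 0.6 | -9 | -3 |
| 0.7 | 0 | 0 |
| 0.8 | +9 | +3 |
| 0.9 | +18 | +6 |
| 1.0 | +27 | +9 |

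Within a column only the case mix changes. With r = 0.90, the range over the same q is -9 to +36 points at u = 0.60 and -27 to +18 points at u = 0.80.

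**Step 4. The same results reported separately, u = 0.70.** These do not depend on q.
- r = 0.90: 0.90 × 0.30 = +27 points when the output is right; -0.90 × 0.70 = -63 points when it is wrong (0.70 to 0.07).
- r = 0.30: +9 and -21 points.

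**Step 5. Equal averages, different behaviour, q = 0.9 and u = 0.70.**
- Indiscriminate, r = 0.90: 0.9 × 0.97 + 0.1 × 0.07 = 0.88.
- Selective, with accuracy 0.90 when the output is right and 0.70 retained when it is wrong: 0.9 × 0.90 + 0.1 × 0.70 = 0.88.

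Both gain 18 points on average, so a comparison of overall means does not separate them. Accuracy in wrong-output cases is 0.07 against 0.70.

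**Step 6. Precision.** With 24 paired clinicians, 80% power at two-sided 0.05 needs a standardised paired difference of about 0.60. That is for the overall comparison; the wrong-output subset has fewer cases behind it.

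**The case against.** The strongest reply is that accuracy is scored against a correct answer, so following a wrong output already counts as an error. A reader might infer that the plan scores over-reliance as benefit. For accuracy that is not so: each followed error lowers the CDS result, and when q > u the higher average is a true net effect for that case mix. This part of the reply stands. What remains is that the net effect belongs to a case mix the plan does not control.

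A reader might also infer that high trust is a success criterion. The Results and Principal Results sections state expectations, and the Outcomes section only says that trust will be measured. No threshold or decision rule exists. What can be said is that both statements of expectation read higher trust as favourable without reference to correctness.

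A third tempting reading is that training patients will be used as cases, which would make outputs look unusually accurate. No section says so. The AI Model Development and Validation section splits data by patient to avoid leakage, and the simulation follows validation. The protection is simply not carried into the description of the case set.

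Nor does the expected AUROC give an error rate for this tool. An equal-variance binormal model with one balanced cut-off turns 0.85 into Phi(0.733) = 0.77 correct, or about 23% wrong. But 0.85 is a stated minimum for CSPH alone, the cue has two thresholds, and the tool covers other domains. The 23% and any overstatement computed from it are not supported.

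Finally, the full protocol or analysis plan may specify case construction, and a breakdown by correctness needs no new data if wrong-output cases are present. The point therefore rests on what the article does fix: an unstratified paired comparison, complexity as the one named matching feature, and higher trust as the expected good result. General monitoring and debriefing do not quantify reliance on wrong outputs.

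**Conclusion.** The point holds as a cheap improvement. As described, the overall accuracy gain depends on an uncontrolled share of wrong-output cases, and neither it nor the trust score can distinguish appropriate from indiscriminate reliance. The algebra needs only the simple reliance model above. The numbers, such as -18 to +27 points at u = 0.70 and r = 0.90, are illustrative, because the documents give no case numbers, unaided accuracy or reliance rates. It does not follow that the planned accuracy result is invalid, that it rewards every form of over-reliance, or that the tool will harm decisions. Recruitment had not begun when the article was submitted, so the change can still be made at the design stage.

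**What to change.** **Randomization section (case construction).**
- Build the simulation cases from patients not used in model training.
- Prespecify the share of cases with a wrong output and balance it across the two case sets, alongside complexity.
- Define output correctness against the reference standard for the dual-threshold CSPH cue, including how cases between the two thresholds are classed.
- Fix the share by design rather than rely on a random draw. As an illustration, with 10 cases per period and a 23% error share (both assumed), 0.77^10 = 0.07 of random sets would contain no wrong output.

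**Statistical Analysis section.**
- Keep the overall paired comparison, and weight the overall accuracy result to the error share seen in held-out validation.
- Add accuracy by condition separately for right-output and wrong-output cases. Usual-care cases can be classed by the output the tool would have shown.
- Report the share of wrong outputs followed under CDS, and interpret trust scores beside these results.

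**Cost.** A case-selection rule and one further breakdown of data already being collected, with no extra clinicians. The wrong-output estimates will be imprecise with about 24 clinicians and should be reported descriptively with confidence intervals.

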## Discussion

### Principal Results

This protocol describes a multiphase study aimed at improving the management of PBC through an explainable AI framework. The anticipated results include a dynamic disease activity index that integrates biochemical, elastography, and patient-reported data, offering superior responsiveness and calibration compared to conventional monitoring. The predictive model is expected to achieve high discrimination for CSPH and outperform existing criteria, reducing unnecessary endoscopies while maintaining patient safety. Finally, the CDS prototype is designed to enhance clinician adherence to guideline-based care, improve decision accuracy, and reduce cognitive load, with usability and trust scores meeting or exceeding established benchmarks.

### Limitations

Several limitations must be acknowledged. The study relies on data from hepatology clinics affiliated with academic centers, which may limit generalizability to community settings. The observational component depends on accurate and complete longitudinal data, and missing data could introduce bias despite planned imputation strategies. Additionally, the implementation phase uses simulated cases before real-world deployment, which may not fully capture the complexity of clinical workflows. Finally, while explainability frameworks are incorporated, clinician adoption of AI tools may still be influenced by factors beyond technical performance, such as institutional culture and resource constraints.

### Comparison With Prior Work

Previous efforts in PBC management have focused primarily on biochemical monitoring and static risk scores such as UK-PBC and GLOBE, which do not account for dynamic symptom burden or integrate noninvasive imaging markers. Similarly, consensus criteria provide useful surrogates for portal hypertension but lack individualized predictive capability. Machine learning models have shown promise in chronic liver disease, yet most operate as opaque systems, limiting clinician trust and adoption. This study builds on these foundations by introducing an explainable, multi-signal approach that combines objective and patient-reported data, integrates noninvasive imaging, and operationalizes insights through EHR-based decision support.

### Conclusions

If successful, this study will demonstrate the feasibility and clinical utility of an explainable AI framework for PBC care, offering a scalable model for precision hepatology. By improving monitoring, risk prediction, and adherence to evidence-based management, the AIm-PBC system has the potential to reduce symptom burden, prevent complications, and enhance quality of life for patients. Future research will focus on external validation across diverse populations and health systems, as well as exploring integration with emerging biomarkers and digital health technologies to further refine predictive accuracy and patient engagement.
